## Abstract

**Background:**

Emerging digital tools play an innovative and key role in supporting women’s psychological well-being throughout the different stages and challenges of cancer. The development and adoption of digital interventions, including chatbots and virtual coaches within smartphone apps, are increasingly recognized as valuable resources for enhancing women’s mental health.

**Objective:**

The aim of this paper is to present the research protocol for a pilot study designed as a proof-of-concept investigation. The study evaluates the feasibility, acceptability, and perceived utility of a mobile app delivering an acceptance and commitment therapy–based stress management intervention. The intervention is delivered through ALBA (A Well-Being Assistant), a virtual coach embedded within the TreC (an acronym for *cartella clinica del cittadino*, meaning “citizen’s electronic health record”) research platform—a mobile health ecosystem designed to support research and digital health interventions. ALBA guides users through 5 coaching sessions tailored for women undergoing breast cancer (BC) treatment. The chatbot-delivered app is an adaptation of Self-Help Plus, a World Health Organization (WHO)–validated stress management intervention, and is provided in text, audio, and video formats. The intervention’s potential impact on participants’ psychological well-being is also explored.

**Methods:**

A convenience sample size of 50 participants will be identified to meet the study’s objectives. Participants will be recruited using a convenience sampling approach from women receiving care at the Breast Unit of the Azienda Provinciale per Servizi Sanitari di Trento. ALBA will interact with the participants for 6 weeks. Specifically, there will be 1 coaching session per week, followed by weekly assigned acceptance and commitment therapy exercises to be performed between sessions.

**Results:**

The app is expected to demonstrate high usability and engagement, aligning with the WHO Self-Help Plus protocol. Improvements in psychological well-being and quality of life are anticipated. Data from this pilot will be analyzed using both quantitative and qualitative methods, with a focus on assessing feasibility, acceptability, and perceived utility and usability in supporting women during BC treatment.

**Conclusions:**

Existing literature indicates a promising role for new technologies in delivering validated mental health interventions, highlighting the potential of digital interventions to address barriers related to social stigma and seeking assistance. This pilot is expected to provide valuable insights on the potential acceptability and usefulness of providing consistent mobile health psychoeducational support to women throughout the course of BC.

**International Registered Report Identifier (IRRID):**

PRR1-10.2196/65837

## Introduction

### Overview

A growing need for psychological support is emerging among the general population, and this need increases even more if we consider populations exposed to stressful situations [1,2]. Emerging scientific literature highlights that psychological vulnerability is often linked to specific periods along the disease trajectory, such as those experienced by women with breast cancer (BC). On the one hand, psychological distress, including stress, anxiety, and depression, often accompanies pathologies such as BC [3]. On the other hand, having a more positive attitude contributes to disease management and recovery, highlighting the importance of addressing mental health issues on physical aspects while taking charge [4,5]. Therefore, improving the mental well-being of women dealing with BC could be an effective way to enhance their overall health. In this sense, evidence of the effectiveness of psychological interventions aimed at women with BC is increasing [6,7], but access to support services still presents several challenges. Many women face geographical barriers, with specialist centers often located far from their homes. Furthermore, the shortage of qualified personnel, such as psychologists, limits access to specialist care. The stigma associated with mental health problems can also prevent women from seeking psychological support in these circumstances [8,9].

Within this framework, there is a recent focus on the potential contributions of digital technologies in fostering psychological well-being, recognizing their capability to provide an optimal solution to reduce barriers [10] and enhance patient empowerment [11].

Indeed, the World Health Organization (WHO) has implemented a comprehensive mental health strategy grounded in principles of inclusivity and scalability, which also incorporates the use of digital technologies [12,13]. The study described in this protocol is part of the panorama of WHO’s strategies, and it aims to evaluate the acceptability and feasibility of an intervention delivered via digital tools to promote psychological well-being. In particular, this intervention, initially validated by WHO itself and called Self-Help Plus (SH+) [14-16], has never been used on the target population of this study, women with BC. SH+ is a low-intensity and transdiagnostic intervention that is easily adaptable in different contexts, delivered by nonspecialist operators, and has solid evidence-based psychological principles inserted in a self-help approach. This approach has already been validated with various populations considered vulnerable, such as migrants, refugees, and health care workers, both to promote psychological well-being and for clinical intervention purposes, demonstrating general acceptability and potential effectiveness [16,17]. The first attempt was made to make the protocol web based within the RESPOND (preparedness of health systems to reduce mental health and psychosocial concerns resulting from the COVID-19 pandemic) project, but the involvement of a human person, in the role of a helper, was still necessary [18].

Cognitive behavioral therapy (CBT) techniques, and in particular those referring to third-generation therapy, are shown to be more suitable than other psychotherapeutic approaches to be transferred into low-intensity interventions delivered by nontraditional methods such as eHealth applications [19]. SH+ is based on the principles of acceptance and commitment therapy (ACT), a third-wave form of CBT [20,21], and is divided into 5 chapters that address 5 strategies for managing stress and promoting psychological well-being. The five chapters, later translated into sessions, are (1) grounding (mindfulness), (2) unhooking (defusion), (3) acting on your values (values-based behavioral activation), (4) being kind (gratitude), and (5) making room (acceptance).

### This Study

#### Overview

Our study is placed within the design and development cycle of the Obesity-Related Behavioral Intervention Trials (ORBIT) model [22], specifically in phase 2a, “refine.” It involves providing material based on SH+ intervention in text, audio, and video format by a virtual coach (ie, a digital chatbot assistant, identified as ALBA [A Well-Being Assistant]) implemented within the TreC (an acronym for *cartella clinica del cittadino*, meaning “citizen’s electronic health record”) research app (a platform or app purposively designed to enable the delivery of several types of mobile health [mHealth] features). It could be stated that this study is innovative for 2 main reasons. First, it involves the digitalization of an intervention that was originally delivered in person and in group settings [14,15]. The ALBA chatbot version is designed to be more accessible and tailored to the individual, functioning without the presence of a helper, unlike in the RESPOND project [17,18], and includes chatbot-guided activity completion between sessions, which differs from the group session delivery format. Therefore, it is essential to evaluate how effectively this new format achieves these goals. Second, this study introduces a novel focus on a population consisting exclusively of female individuals and those considered medically vulnerable, which represents a significant new factor in evaluating the feasibility, acceptability, and efficacy outcomes. The proof-of-concept (POC) study, described in this research protocol, aims to test both the transferability and acceptability of the digitalized intervention from the original, context-specific in-person format (refer to the Primary Objective section), as well as to assess its initial efficacy on the targeted psychological variables in this newly defined population (refer to the Secondary Objective section).

#### ALBA Intervention

ALBA is an intervention based on ACT techniques; it aims to promote the quality of life and enhance stress-coping skills in women with BC through a psychoeducational approach. The module is self-administered and available for both Android (Google LLC) and iOS (Apple Inc) devices. All the contents of the dialogues were developed by a group of researchers belonging to the Digital Health Research of the Bruno Kessler Foundation of Trento and psychologists belonging to the Pavoniano Artigianelli Institute with specific skills in the communication field starting from the SH+ manual [23] and subsequently reviewed by a psychologist manager of the psychology operational unit of the Provincial Health Services Authority of Trento (Azienda Provinciale per i Servizi Sanitari di Trento). The dialogues, videos, and audio tracks were developed according to educational logic. Furthermore, the structuring of the material and the delivery methods were supervised by professionals from the WHO Center for Research in Mental Health of the University of Verona, who have already carried out implementation studies and validation of SH+ at national and international levels.

To ensure the best possible adaptation of the intervention to our target sample, we previously conducted a co-design study based on guidelines of a previous step of the ORBIT model [22]. This process involved domain experts, such as psychologists, SH+ experts, and communication and usability experts, and a small sample of women with BC and oncological clinicians. For further details, please refer to our previous study [24].

#### Technological Tools

This intervention is part of a behavior change framework [25] aimed at supporting women’s psychological well-being. The term “intervention” refers to the virtual coach, the chatbot ALBA, which delivers structured, rule-based informational content reviewed by psychological professionals. ALBA functions as a tool for information delivery, not as a conversational agent, as it does not engage in real-time, dynamic interactions. While it collects and transmits data, it is primarily a chatbot for eHealth interventions. ALBA is developed for research purposes to validate the digital health version of SH+ focused on ACT practices for women with BC.

ALBA, the technological component of this study, is built upon the general TreC platform, a public mHealth platform enabling residents of the Autonomous Province of Trento (North Italy) to access, manage, and share their health and well-being information. TreC is a robust and reliable platform designed as a “system of systems” rather than merely a data repository [26]. Indeed, its flexible architecture allows for collecting and managing diverse data types and supports developing and integrating additional subsystems to offer specific functions. A key feature of TreC is empowering users to manage their health-related data, functioning as a personal health record.

Within this general platform, a specific mHealth ecosystem has been designed to support research and digital health interventions, called TreC research (“Trec Ricerca” in Italian; Figure 1). This module is available for free download as a mobile app to all women diagnosed with BC. Authentication is required via the secure, General Data Protection Regulation–compliant national identification system (Sistema Pubblico di Identità Digitale).

**Figure 1 figure1:**
[figure not shown]
Graphical representation of the TreC (an acronym for cartella clinica del cittadino, meaning “citizen’s electronic health record”) research platform, which incorporates the ALBA (A Well-Being Assistant) chatbot and illustrates its interactions with the database and users. SH+: Self-Help Plus.

#### SH+ Sessions

The intervention spans a total duration of 6 weeks. For each week, a session of approximately 40 minutes is delivered, while this can be divided into two 20-minute subsessions according to users’ preferences. Phase 3, represented in Figure 2, provides a graphical depiction of the conversational protocol delivered to the participants and its chronological structure. The intervention’s contents are presented through a gradual process designed to progressively increase the participant’s self-awareness and mindfulness-oriented skills, including accepting and normalizing internal states, managing stress, and enhancing psychological well-being. Participants are also required to complete tasks and fill in a dedicated e-diary. The program is structured into 5 main coaching sessions, following the operational chapters of the SH+ manual, each addressing a specific strategy for managing stress and promoting psychological well-being, which are the main aims of the intervention. These 5 modules, translated into weekly e-sessions, are grounding (mindfulness), unhooking (defusion), acting on your values (values-based behavioral activation), being kind (gratitude), and making room (acceptance; phase 3 in Figure 2).

**Figure 2 figure2:**
[figure not shown]
Graphical representation of the conversational protocol delivered to users and its chronological structure. COPE-NVI-25: Coping Orientation to the Problems Experienced; ERQ: Emotion Regulation Questionnaire; GHQ: General Health Questionnaire; GSE: General Self-Efficacy Scale; ITA BUS B: Italian Chatbot Usability Scale, version B; K-10: Kessler Psychological Distress Scale; MPFI: Multidimensional Psychological Flexibility Inventory; PSS: Perceived Stress Scale; SF-36: Short Form Health Survey 36; SUS: System Usability Scale; UES-SF: User Engagement Scale-Short Form; uMARS: User Mobile Application Rating Scale.

### Goal of the Study and Research Questions

#### Overview

Therefore, this protocol paper aims to describe the POC developed to deploy the ALBA app to women with a BC diagnosis. The POC aims to evaluate the acceptability and feasibility of delivering SH+ through ALBA, a platform designed to provide ACT-based psychoeducational sessions. ALBA supports users in completing exercises and tasks assigned between coaching sessions and periodically delivers structured information—curated by professional psychologists—in audio, text, and video formats. This material is independently accessed and managed by users. The virtual coach serves as an information transmission tool, while the app also administers questionnaires and manages data collection.

This behavioral change intervention [25] aims to empower women with adaptive strategies for managing stress. Studying its feasibility can represent a first step to evaluate the possibility of including a digital service to support and promote psychological well-being in the context of stepped care for women in the BC pathway.

#### Primary Objective

The main objective of the POC study is to evaluate how women experience the chatbot-based version of the WHO-validated intervention SH+. It aims to assess the following areas: (1) the user experience (UX) and the usability of the virtual coach, ALBA, installed in the TreC research app environment and (2) how users felt during the intervention, using ALBA, as reported through semistructured interviews. The IT evaluation of the TreC research app itself will be presented in another study.

#### Secondary Objective

The secondary goal is to assess the efficacy of the intervention on women’s psychological well-being through the administration of self-report pretest-posttest and follow-up questionnaires.

## Methods

### Design and Study Plan

The study is articulated in 4 main phases depicted in Figure 2 and extensively described in the Data Collection section.

#### Phase 0: Recruitment

This phase will take place at the hospital’s Breast Unit, and it will be carried out by the health professionals of the Breast Unit (physicians and case manager nurses).

#### Phase 1: Screening

The screening phase is carried out by psychologists, and subsequent included participants are given access to the TreC research app.

#### Phase 2: Enrollment at Week 0

At the beginning of the path, ALBA will administer 5 self-report questionnaires to establish the baseline level of the examined variables (preassessment questionnaires). The participant can choose the best day and time to interact with ALBA (first interaction with ALBA).

#### Phase 3: Intervention Delivery From Week 1 to Week 5

Specifically, there is 1 psychoeducational session per week, and the contents will be presented in different formats (text, images, audio, and video tracks). Moreover, ALBA provides users with instructions on how to carry out simple exercises and fill in a personal diary. The questionnaires will be further administered by ALBA at the end of the course (at week 6) to verify whether participants have perceived a change in terms of psychological well-being and quality of life. In total, 4 questionnaires will be administered to evaluate usability and UX (weeks 3 and 6).

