### Study Outcomes

#### Primary Outcomes

The primary outcomes are UX and usability. They will be assessed using 4 questionnaires, namely, the User Engagement Scale-Short Form (UES-SF) [34], the System Usability Scale (SUS) [35], the Italian Chatbot Usability Scale, version B (ITA BUS B) [36], and the User Mobile Application Rating Scale (uMARS) [37]. They will be administered at different time slots throughout the study, in particular, at the end of week 3 (UES-SF, SUS, and ITA BUS B) and at the end of the study (week 6: UES-SF, SUS,; ITA BUS B, and uMARS; Textbox 2).

Summary of the questionnaires administered and their timing.

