#### Phase 1: Screening

To fulfill the verification of the inclusion criteria from 7 to 9 and the exclusion criteria 5 and 6, the researchers will administer the screening questionnaires through LimeSurvey (LimeSurvey GmbH; Textbox 2).

After processing the results of the screening questionnaires and the various sociodemographic inclusion criteria, the women will be contacted again, and the following scenarios will open.

First, the participant does not meet the inclusion criteria due to demonstrating a markedly positive state of psychological well-being, as indicated by a stress level <15.9 on the Kessler Psychological Distress Scale (K-10) [28], a general well-being score <3 on the General Health Questionnaire (GHQ) [39], and a general well-being score >80 on the “Mental Health” scale of the Short Form Health Survey 36 (SF-36) [29]. In such cases, the women will not be enrolled in the study, and the reasons for exclusion will be shared along with the screening questionnaire results, but upon the participant’s request.

Second, the participant does not meet the inclusion criteria due to exhibiting a markedly negative state of psychological well-being or signs of psychopathology, as indicated by a score <30 on mental health scale of the SF-36 and a K-10 score >29.9. In addition, in the second case, the participant will not be able to be enrolled in the study, and the reasons for exclusion from the study will be returned, and only upon request of the participant will the results obtained from the screening questionnaires be returned. Furthermore, indications of local services to contact for problems will be appropriately provided. This is to provide the participant with a structured and agreed system of referral to a qualified support service and taking charge where appropriate.

Third, the participant meets the inclusion criteria. In this case, the participant is enrolled in the study. The participant will also be asked if they would like to participate in a qualitative interview and in compiling a last questionnaire about stress 4 months after delivery. In case of positive feedback, the telephone number will be collected to facilitate contacts and follow-up interviews.

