#### Phases 2 and 3: Enrollment and Participation

##### Overview

To properly assess included participants’ experience during the psychoeducational pathway, some questionnaires were adopted and delivered at the beginning (phase 2), during, and at the end of the interaction with ALBA (phase 3), as shown in Textbox 2.

Specifically, 5 questionnaires will be administered at the beginning (week 0) and at the end of the intervention (week 6) together with the initial screening questionnaires, which aim to investigate stress level, self-efficacy, emotional regulation, psychological flexibility, coping strategies, well-being, and level of psychological well-being. None of these questionnaires has diagnostic purposes. Therefore, they will not be used to diagnose psychopathology but only to collect descriptive data.

Four more questionnaires will be sent during the process to analyze the usability and involvement of the participant with the app and with the virtual coach, ALBA. Specifically, the usability and UX questionnaires will be administered at the end of week 3 (3 questionnaires) and week 6 (4 questionnaires).

A detailed description of each instrument that will be administered is presented in the subsequent sections.

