### Data Analysis

#### Overview

Preliminary data analysis is scheduled for early November 2024, while the final results will be available at the end of the study. The publication of the results will take place within 1 year after the conclusion of the study. Given the potential for dropout, which is commonly observed in digital interventions, and the sensitive nature of our sample population, missing data will be carefully addressed during the analysis phase. Where appropriate, multiple imputation methods will be applied to account for missing values and reduce potential bias. In addition, participants who drop out or fail to complete the follow-up assessments will be included in the analysis using an intention-to-treat approach, wherever feasible.

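### The article describes no route outside the app for collecting week-3 and week-6 scores from women who stop using ALBA, so those scores are likely to be missing for reasons tied to the outcomes

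*Protocol article*

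**What the plan says.** **Channel for the psychological scales.** Under Design and Study Plan, Phase 2, "ALBA will administer 5 self-report questionnaires to establish the baseline level of the examined variables". Under Phase 3 of the same section, "The questionnaires will be further administered by ALBA at the end of the course (at week 6"). The Overview of Goal of the Study and Research Questions adds that "the app also administers questionnaires and manages data collection".

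**Channel for the usability scales.** Under Study Outcomes, "The primary outcomes are UX and usability". UES-SF, SUS and ITA BUS B are given at weeks 3 and 6, and uMARS at week 6. The Overview of Phases 2 and 3 (Data Collection) says "Four more questionnaires will be sent during the process to analyze the usability and involvement of the participant with the app", without naming how they are sent.

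**Channels outside the app.** At screening, "the researchers will administer the screening questionnaires through LimeSurvey". For women who agree to the four-month interview and stress questionnaire, "the telephone number will be collected to facilitate contacts and follow-up interviews". LimeSurvey is not mentioned for any later time point.

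**Unfilled questionnaires.** The last paragraph of Psychological Assessment deals with a woman who leaves activities and questionnaires incomplete. What she experienced and how she used the platform will be explored at the postintervention interview. The only such interview described takes place four months after the intervention, with women who consented to it.

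**Analysis.** Data Analysis, Overview, foresees multiple imputation where suitable and says that "participants who drop out or fail to complete the follow-up assessments will be included in the analysis using an intention-to-treat approach, wherever feasible".

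**The concern.** In a single-arm study the pre-post change is all the efficacy evidence there is, and the usability scores are the primary outcomes. Both are to be collected through, or evidently through, the product being judged. A woman who finds ALBA awkward or unhelpful and stops opening it is less likely to be measured at week 6 than one who likes it. Her absence would then carry information about the score she would have given.

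An intention-to-treat analysis needs either observed outcomes from such women or a credible model for the missing ones. Without a second route, the model would have to borrow from women who stayed, under an assumption that the data cannot check. The Results section lists changes in psychological variables, acceptability and usability among the benchmarks for moving to a larger trial, so a favourable tilt could affect that decision. This is a matter of data collection: no analysis plan written later can recover week-6 scores that were never asked for by another route.

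**Working it through.** **Step 1. What a woman who stops using the app before week 6 would have on record, if the plan is followed as written**

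| Item | Described channel | Available from her? |
|---|---|---|
| Week-0 psychological scales | ALBA | Yes |
| Week-3 usability scales | Not named; evidently the app | Only if she stopped after week 3 |
| Week-6 psychological scales (GHQ, PSS, MPFI, GSE, ERQ, COPE-NVI-25) | ALBA | Unlikely |
| Week-6 usability scales | Not named; evidently the app | Unlikely |
| Activity logs | Platform | Yes, up to the point she stopped |
| Four-month PSS | At follow-up, with telephone contact | Only if she agreed to it |
| Four-month interview | Psychologist | Only if she agreed; gives experience, not the missed scores |

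The gap lies in the week-6 scores, and in the week-3 usability scores of early stoppers. The four-month PSS is one of the six psychological scales and is taken at a different time, so it can inform an imputation but does not replace the week-6 value.

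**Step 2. The plan's own figures (Sample Size)**

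Inputs: significance level .025, power 0.80, mean difference 1.00, SD 2.00, dropout 20%, 50 recruited.

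- Effect size: 1.00 / 2.00 = 0.50.
- Paired t test with noncentral t, two-sided .025, power 0.80: n = 41. This matches the stated 41, so the 0.50 is in units of the SD of the change.
- Allowance for dropout: 41 × 1.20 = 49.2, rounded up to 50, as stated. (Dividing instead, 41 / 0.80 = 51.25, gives 52. The difference of two is not the point here.)
- With 20% of 50 lost, 50 × 0.80 = 40 women have an observed week-6 change. Power at 0.50 is then 0.793, so precision is hardly affected. The question is bias.

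**Step 3. How far the observed mean could differ from the all-enrolled mean**

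Let d be the proportion without a week-6 score, m the mean change in women with one, and c the mean change in women without.

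- All-enrolled mean = (1 − d) × m + d × c.
- Observed mean minus all-enrolled mean = d × (m − c).

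Take m = 0.50 SD from the plan. The values of c are assumptions; so is d = 40%, since the article plans for 20%.

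| c (assumed) | All-enrolled mean, d = 20% | All-enrolled mean, d = 40% |
|---|---|---|
| 0.50 SD | 0.80 × 0.50 + 0.20 × 0.50 = 0.50 | 0.50 |
| 0.25 SD | 0.40 + 0.05 = 0.45 | 0.30 + 0.10 = 0.40 |
| 0 | 0.40 + 0 = 0.40 | 0.30 |
| −0.25 SD | 0.40 − 0.05 = 0.35 | 0.30 − 0.10 = 0.20 |

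The same formula applies to a usability score: at 20% missing, the observed mean exceeds the all-enrolled mean by one fifth of the gap between stayers and stoppers.

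**Step 4. What imputation changes**

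The table compares the mean in women with scores against the mean in all enrolled women. The planned estimate is neither. If baseline scores, week-3 scores, logs and the four-month PSS predict the missing values well, imputation would move the estimate from the observed mean towards the all-enrolled mean. If they predict poorly, it would stay near the observed mean. The article gives no figure from which to judge which is closer.

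**The case against.** The strongest reply is that this is a condensed journal article, and that chasing non-responders is operational detail for a full protocol or data-management manual. That would settle the matter if the article were merely silent. It is not: it takes up the case of unfilled questionnaires and gives a remedy, and that remedy does not collect the scores.

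Other parts of the reply stand and limit the point:

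- A reader might infer that the questionnaires exist only inside the app. No section says so, and for the usability scales no channel is named at all. App delivery is the evident reading, not a stated rule.
- A reader might infer that stopping the intervention and leaving assessment are one event. The text does not support that. No section makes the questionnaires conditional on finishing sessions, a woman can skip sessions and still answer, and reminders and other retention features are planned.
- A reader might infer that a woman who stops has no observed outcome. She may have week-3 usability scores, activity logs and a four-month PSS, and agreement to the last is sought at enrollment, before any disengagement.
- A reader might infer that the intention-to-treat analysis reduces to a completer analysis. Multiple imputation can condition on what is known about each woman, and the article qualifies its intention-to-treat statement. A sensitivity analysis for scores missing not at random is commonly left to an analysis plan, which is not at hand, and its absence is not held against the article.
- Engagement, retention and dropout are themselves progression benchmarks, so disengagement counts against ALBA directly and is not hidden.

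**Conclusion.** The point holds as a worthwhile improvement to data collection in a proof-of-concept study. Followed as written, the plan is likely to lose week-6 scores preferentially from women who disengage, and its stated fallback does not recover them. Imputation for these women would lean on a missing-at-random assumption that is doubtful, because the likely reasons for stopping (poor usability, no perceived benefit) are close to what is being measured. Any resulting bias would probably favour ALBA.

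Its size is not known. At the planned 20% loss, with completers changing by 0.50 SD, the all-enrolled mean is 0.50 SD if stoppers change equally and 0.40 SD if they do not change. A reader might take the second case as showing that the effect will be overstated by 25% (0.50 / 0.40 = 1.25). The documents do not support that as an estimate: the zero change is assumed, and the comparison uses the raw mean in completers, not the imputed result.

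The conclusion rests on two readings: that the app is the channel for the usability scales, and that no second route is set out in a fuller document not shown. If such a route exists, the article need only state it.

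**What to change.** Amend Design and Study Plan (Phase 3), the Overview of Phases 2 and 3 under Data Collection, and the last paragraph of Psychological Assessment, to say that:

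- the week-3 and week-6 questionnaires have calendar due dates counted from week 1, regardless of how many sessions were completed;
- any woman who has not completed them in the app within a short fixed window of the due date (for example, 7 days) is sent the same questionnaires through LimeSurvey, under her study code;
- stopping the app does not end outcome collection unless she withdraws consent;
- the channel used is recorded for each questionnaire.

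The cost is setting up existing questionnaires in a survey tool already in use, one further reminder and an amendment. The article collects telephone numbers only from women who agree to the four-month follow-up, so the information and privacy text may need a line to cover this contact for all participants. The downside is mixed app and web completion for a few women, which the recorded channel lets the analysis describe. Some women will still not answer, but fewer scores would depend on imputation.
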